## Abstract

**Introduction:**

Jaundice caused by hyperbilirubinaemia is a physiological phenomenon in the neonatal period. However, severe hyperbilirubinaemia, when left untreated, may cause kernicterus, a severe condition resulting in lifelong neurological disabilities. Although commonly applied, visual inspection is ineffective in identifying severe hyperbilirubinaemia. We aim to investigate whether among babies cared for in primary care: (1) transcutaneous bilirubin (TcB) screening can help reduce severe hyperbilirubinaemia and (2) primary care-based (versus hospital-based) phototherapy can help reduce hospital admissions.

**Methods and analysis:**

A factorial stepped-wedge cluster randomised controlled trial will be conducted in seven Dutch primary care birth centres (PCBC). Neonates born after 35 weeks of gestation and cared for at a participating PCBC for at least 2 days within the first week of life are eligible, provided they have not received phototherapy before. According to the stepped-wedge design, following a phase of ‘usual care’ (visual assessment and selective total serum bilirubin (TSB) quantification), either daily TcB measurement or, if indicated, phototherapy in the PCBC will be implemented (phase II). In phase III, both interventions will be evaluated in each PCBC. We aim to include 5500 neonates over 3 years.

Primary outcomes are assessed at 14 days of life: (1) the proportion of neonates having experienced severe hyperbilirubinaemia (for the TcB screening intervention), defined as a TSB above the mean of the phototherapy and the exchange transfusion threshold and (2) the proportion of neonates having required hospital admission for hyperbilirubinaemia treatment (for the phototherapy intervention in primary care).

**Ethics and dissemination:**

This study has been approved by the Medical Research Ethics Committee of the Erasmus MC Rotterdam, the Netherlands (MEC-2017-473). Written parental informed consent will be obtained. Results from this study will be published in peer-reviewed journals and presented at (inter)national meetings.

**Trial registration number:**

NTR7187.

Strenghts and limitations of this studyThis study is the first randomised controlled trial (RCT) to assess the (cost) effectiveness of transcutaneous bilirubin measurement as a universal screening tool for potentially severe jaundice, addressing a knowledge gap highlighted in several national guidelines.This study is also the first RCT to assess the (cost) effectiveness of phototherapy outside the hospital setting.The stepped-wedge design of this study allows all participating primary care birth centres to have introduced both interventions as standard care towards the end of the study, which will aid implementation if (cost) effectiveness of the interventions is demonstrated.A limitation is that parents and care providers cannot be blinded to allocation of the interventions.

## Introduction

In newborns, severe hyperbilirubinaemia may cause brain damage when it is not recognised or is left untreated.^1 2^ This spectrum of neurological sequelae is called kernicterus spectrum disorder (KSD), with acute bilirubin encephalopathy and its consequences at the extreme end, and more subtle disorders at the other.^1 3^ KSD also encompasses ‘classical kernicterus’, a chronic, irreversible, neuropathological disorder involving neuromotor dysfunction, auditory disorders and oculomotor impairments.^1–4^

In high income countries, an estimated 1 in 67 000 neonates develop classical kernicterus.^5 6^

Timely recognition of potentially severe jaundice, caused by hyperbilirubinaemia, is essential to prevent KSD.^7 8^ Traditionally, jaundice is identified via visual inspection by maternity care professionals, midwives or parents. If potentially severe jaundice is suspected, total serum bilirubin (TSB) is quantified in blood taken via a skin prick to assess the need for treatment.^9^ However, visual inspection of neonatal jaundice is proven to be inaccurate in detecting hyperbilirubinaemia^10 11^ and, therefore, ineffective in preventing kernicterus.^12^

Guidelines in several high-income countries advise universal screening for jaundice in newborns using TSB or transcutaneous bilirubin (TcB) measurement.^10 13^ Several observational studies have shown a good correlation between TSB and TcB measurements in the neonatal period.^14 15^ A programmatic evaluation of a TcB-based screening programme in Canada demonstrated a 55% reduction in severe hyperbilirubinaemia and related healthcare utilisation as compared with visual inspection plus selective TSB quantification.^16^ Similar findings were obtained in a retrospective multicentre study evaluating a screening programme using standard versus selective TSB or TcB measurement in the USA.^17^ Universal screening for neonatal jaundice in the primary care setting has the potential to reduce the incidence of severe hyperbilirubinaemia.^2 18^ This would also bring down the number of patients who require exchange transfusion which is a highly invasive treatment that carries significant health risks and substantial costs.

Hyperbilirubinaemia is usually treated with phototherapy in a hospital setting which may be applied via various modalities.^2^ Fibreoptic phototherapy using an underneath device (ie, mattress) is effective in reducing TSB levels, is safe,^19^ and meets existing guidelines.^9^ There is some evidence to suggest that fibreoptic phototherapy may safely and effectively be used in the primary care setting as well.^14 20 21^ The institution of phototherapy in the primary care setting may reduce the number of neonates admitted to hospital for hyperbilirubinaemia treatment and reduce associated costs.^22^

Whereas universal TcB screening for neonatal hyperbilirubinaemia and phototherapy provided in primary care have the potential to be effective and cost-effective via reducing the incidence of severe hyperbilirubinaemia and the need for hospitalisation.^14 23^ Evidence to support these assertions is currently lacking, while in today’s healthcare arena cost-effectiveness considerations are becoming increasingly important.

We hypothesise that non-invasive screening for neonatal hyperbilirubinaemia using TcB and application of phototherapy in primary care will (cost) effectively reduce the incidence of severe hyperbilirubinaemia and the need for hospital admission for hyperbilirubinaemia treatment. Here, we present our protocol for a factorial stepped-wedge cluster randomised controlled trial (RCT) among newborns cared for in primary care to test these hypotheses.

## Methods and analysis

### Study design

We will conduct a factorial stepped-wedge cluster RCT in seven primary care birth centres (PCBCs) in the Netherlands to evaluate among newborns the effectiveness of (1) screening for hyperbilirubinaemia using daily TcB quantification to reduce the incidence of severe hyperbilirubinaemia and (2) treatment of hyperbilirubinaemia (if indicated) using phototherapy instituted within the PCBC to reduce the need for hospital admission. Accordingly, each PCBC will start with (1) a control phase in which usual care is evaluated, followed by (2) a second phase in which one of both interventions is evaluated, followed by (3) a final phase in which both interventions are evaluated in parallel. More detail is provided below.

### Dutch perinatal care system

In the Netherlands, a significant proportion of women (30% in 2016) give birth in a primary care setting (ie, at home or in a PCBC) under the supervision of a community midwife.^24^ In addition, many who deliver in a hospital setting are discharged home or to a PCBC within 24 hours after delivery. Maternity care assistants provide maternity care when the neonate and the mother are at home or in a PCBC, under the supervision of the community midwife (who will visit at least three times in the first week).^25^ Only healthy neonates will be cared for at home or in a PCBC (ie, neonates with congenital infection or other diseases will receive initial treatment in the hospital). The community midwife will consult the paediatrician of an affiliated nearby hospital if a potential clinical problem such as hyperbilirubinaemia presents in the neonate. Neonates with a gestational age (GA) above 35 weeks who have been discharged from the hospital are especially at risk of developing severe unconjugated hyperbilirubinaemia.^26^

### Participants

#### Study sites

This study will be performed in seven PCBCs in the Netherlands. In these PCBCs altogether approximately 5000 neonates and their mothers are admitted for at least 48 hours each year. Each of the five largest PCBCs will be considered a cluster in the context of our cluster RCT. The two smallest PCBCs will be paired and will form a cluster together. A PCBC was selected for the study if it facilitated provision of maternity care during the first days post partum (that is, some PCBCs only facilitate deliveries and do not provide care beyond the first 24 hours after delivery).

#### Patient eligibility

Neonates are eligible for inclusion in the study if:The neonate was born after 35 completed weeks of gestation. Note: only neonates with a GA of 37 weeks or higher are born in primary care; nevertheless, a neonate may be eligible when born in the hospital between 35 and 37 weeks of GA and then discharged to a PCBC within 7 days after birth.The neonate is admitted to a participating PCBC within the first week of life.The neonate is expected to remain admitted for at least 2 days (to allow for serial TcB measurements to take place).Signed informed consent **(I**C) is provided by parent(s) or primary caregiver(s).

Neonates are not eligible if:The neonate received phototherapy previously or is currently receiving phototherapy (reliability of TcB measurement is reduced in neonates who are receiving or have received phototherapy).^14^
Parents do not have sufficient understanding of the Dutch language to be able to comprehend the patient information sheet and questionnaire.

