### Randomisation and blinding

Each of the participating PCBCs will be randomised to one of the predefined timelines (as depicted in figure 2 above) by an online randomisation module (www.randomization.com). The two smallest PCBCs will be paired and randomised to the same timeline (see figure 2).

Given the nature of the treatment in the intervention groups and the control group, blinding of participants (and parents) and healthcare personnel is not possible. Analyses will be performed by a researcher who is blinded to the PCBC allocation scheme.

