### Study procedures

All PCBCs in the Netherlands that provide maternity care to mothers and neonates in the first days after delivery were invited to participate. Eligibility of neonates admitted to the PCBC will be assessed by the maternity care or study personnel based on the inclusion and exclusion criteria. IC of parents will be obtained by the maternity care professional. Research nurses and study personnel will support the maternity care professionals in obtaining IC and collecting data.

Depending on the allocation and the moment of admission in the PCBC during the study period, the neonate is included in the control period, in a time period where one of the interventions is implemented, or in a time period where both interventions are implemented. Standard operating procedures (SOPs) for each study phase have been developed.

Maternity care personnel of all PCBCs will be trained in the SOPs and in using the transcutaneous bilirubinometer and the phototherapy mattress to ensure the interventions are applied in a professional standardised manner. For this purpose, an e-learning module has been developed (available from: https://xoteur.12change.eu/play.php?template_id=798); in addition, during the study period three training sessions for maternity care professionals are held at each PCBC prior to the start of each subsequent study phase (ie, intervention implementation).

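### Eligibility and consent are not tied to a point before bilirubin status is known, so unblinded staff could enrol high-risk neonates differently by phase

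*Protocol article*

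**What the plan says.** All references are to the protocol article.

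- **Patient eligibility.** Besides gestation and consent, inclusion needs two conditions: "The neonate is admitted to a participating PCBC within the first week of life" and "The neonate is expected to remain admitted for at least 2 days". The exclusions are insufficient Dutch and "The neonate received phototherapy previously or is currently receiving phototherapy". The reason given for the phototherapy exclusion is the reliability of transcutaneous (TcB) readings, not selection.
- **Study procedures.** "Eligibility of neonates admitted to the PCBC will be assessed by the maternity care or study personnel", and "IC of parents will be obtained by the maternity care professional". The phase a neonate belongs to is set "Depending on the allocation and the moment of admission in the PCBC during the study period".
- **Randomisation and blinding.** "blinding of participants (and parents) and healthcare personnel is not possible".
- **Control group and Intervention 2.** In control, a baby needing treatment is admitted to hospital. In phototherapy phases the birth centre is the default place of treatment.
- **Intervention 1.** Daily TcB is measured in the included neonates.
- **Primary outcomes.** Both are counted over the first 14 days of life, so a severe TSB measured before consent can count.
- **Statistical analysis.** Intention-to-treat, with generalised linear mixed models for period and clustering.

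**The concern.** The person seeking consent knows the phase and may know, from skin colour or a test result, that the baby is likely to have an outcome event. Nothing in the published criteria prevents enrolment on that knowledge.

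There are two routes by which enrolment could differ by phase:

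- **Expected stay.** Take a baby not yet enrolled who is found above the phototherapy threshold. Without birth-centre phototherapy, that baby is about to leave for hospital and may fail the two-day criterion. In a phototherapy phase the same baby is expected to stay and can meet it. Staff who apply the rule honestly would still enrol differently.
- **Incentive.** TcB is given to included neonates, so a visibly jaundiced baby gains a measurement by being enrolled in a TcB phase and gains nothing comparable in control.

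Both routes would raise the share of high-risk neonates in intervention phases relative to control. The event rate there would rise for reasons unrelated to the intervention, and a real benefit would be understated or missed. Intention-to-treat applies only to those enrolled, and period and cluster terms do not adjust for who was enrolled. The Discussion acknowledges that unblinded staff may act differently, but only in care and testing.

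**Working it through.** **1. The plan's own figures.** Inputs from Sample size: 1.2% v 0.5% severe hyperbilirubinaemia, 4% v 2% admission, two-sided 0.05, power 80%. With n per arm = (1.96 + 0.8416)² × [p1(1−p1) + p2(1−p2)] / (p1−p2)²:
- Severe cases: 7.849 × (0.011856 + 0.004975) / 0.007² ≈ 2696. The protocol states 2691.
- Admission: 7.849 × (0.0384 + 0.0196) / 0.02² ≈ 1138. The protocol states 1136.

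Both reproduce to within 0.3%. At 2691 per arm the expected severe cases are 2691 × 0.012 ≈ 32 and 2691 × 0.005 ≈ 13, so a handful of selectively enrolled babies matters.

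**2. Room for selection.** Study sites gives "approximately 5000 neonates and their mothers are admitted for at least 48 hours each year", and inclusion lasts 2.5 years per centre. 5000 × 2.5 = 12,500 admissions, and 5500 / 12,500 = 44%. Over the 3 years in the abstract it is 5500 / 15,000 = 37%.

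**3. Enrichment factor.** Let r be how many times as readily a neonate who will need phototherapy (4%, from Sample size) is enrolled compared with others. The documents give no r; 1.2, 1.5 and 2 are assumptions. The share of such neonates among those enrolled is multiplied by f = r / (0.04r + 0.96):
- r = 1.2: 1.2 / 1.008 = 1.190
- r = 1.5: 1.5 / 1.02 = 1.471
- r = 2: 2 / 1.04 = 1.923

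Both outcomes arise within this group, so event rates scale by f.

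**4. What reaches each estimate.** The comparator for each intervention is not pure control: periods without TcB include phototherapy-only periods, and the reverse.

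- *All intervention phases equally enriched.* In a balanced 2×2 with main effects on the log scale, the main effect averages a contrast shifted by log f (one intervention v control) and one shifted by 0 (both v the other alone). Half of log f remains, so the apparent RR is the true RR × √f, with √f = 1.091, 1.213, 1.387.
- *Only phases with that intervention enriched.* The apparent RR is the true RR × f.

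True RRs are 2/4 = 0.50 and 0.5/1.2 = 0.417.

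| r | Admission, all phases | Admission, that intervention only | Severe, all phases | Severe, that intervention only |
|---|---|---|---|---|
| 1.2 | 0.55 | 0.60 | 0.45 | 0.50 |
| 1.5 | 0.61 | 0.74 | 0.51 | 0.61 |
| 2 | 0.69 | 0.96 | 0.58 | 0.80 |

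(Rounding the severe-case RR to 0.42 first turns 0.45 into 0.46.)

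**5. The stay criterion alone.** It follows the phototherapy factor, so it acts on the admission outcome. If phases without birth-centre phototherapy fail to enrol 10% or 25% of their admission cases (assumed), the rate there is 0.036 / 0.996 = 3.61% or 0.030 / 0.990 = 3.03%. The true 0.50 then appears as 2 / 3.61 = 0.55 or 2 / 3.03 = 0.66.

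**The case against.** The strongest reply is that a condensed article is being read for what it omits. Consent timing and screening logs may be fixed in the full protocol or in the standard operating procedures that the article mentions. First-week admission and the expected stay already give some bound. That part stands: a reader might infer that enrolment is allowed at any time until phototherapy starts, but the article does not say so; it only sets no earlier limit. What remains is that the published criteria, followed as written, let the same baby be enrollable in one phase and not in another.

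Four other inferences go too far.

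- **That inclusion is the route to birth-centre phototherapy.** Only TcB is described as limited to included neonates; Intervention 2 has no such limit. In a TcB-only phase, a baby whose TSB is already above threshold gains nothing from enrolment.
- **That the full factor f is the expected bias.** It ignores the factorial comparators and is the upper case in the table.
- **That 44% shows selection.** The 5000 a year are admissions, not eligible and consenting families, and 5500 is a target, not a cap. Non-enrolment may be unrelated to jaundice.
- **That a false claim of benefit is likely.** The described selection works against the interventions. For admissions it weakens further if the extra babies are managed wholly in the birth centre, because they then enter only the denominator.

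**Conclusion.** The point holds as a weakness in the published eligibility and consent rules. Phase is known before consent, unblinded staff take consent, bilirubin status may already be known, and the stay criterion can depend on phase. The documents show an opportunity for phase-dependent enrolment, not that it occurred.

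The likely direction is against both interventions. The size is unknown. For assumed r of 1.2 to 2, an admission RR of 0.50 would appear as 0.55–0.69 under equal enrichment of all intervention phases, and as 0.60–0.96 at most. A severe-case RR of 0.42 would appear as 0.45–0.58, and as 0.50–0.80 at most. These ranges assume a balanced 2×2 layout (the allocation figure is not shown), a 4% high-risk share, and all events arising in that group. They ignore the time structure of the stepped wedge. The severe-case figures depend on the enrolment incentive, because the stay criterion follows the phototherapy factor and would largely cancel from the TcB contrast in a balanced layout.

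**What to change.** - In every phase, require eligibility assessment and consent at or soon after birth-centre admission and before any TSB or TcB there. Judge expected stay without regard to bilirubin status.
- Record the date and time of consent.
- Report admitted, eligible and included counts by phase.
- Add a sensitivity analysis of both primary outcomes that excludes neonates whose first bilirubin test preceded consent.

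This governs enrolment only and changes no test or treatment. It costs an eligibility clause, a time field, a register count and one extra analysis. Some late-identified neonates would be lost. Selection on visible jaundice before consent would be reduced but not eliminated, which is why the counts by phase are needed as well. If the full protocol or the operating procedures already fix consent timing, stating that rule in the eligibility section would settle that part.

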### Interventions and control

In this study, two interventions will be assessed in a 2×2 factorial design to determine the effectiveness of each intervention separately. The timing of the implementation of each intervention will be allocated at the PCBC level.

#### Control group: usual care

During this initial study phase, usual care will be evaluated. Accordingly, visual inspection is used to identify jaundice, as advised in the Dutch national guideline for neonatal hyperbilirubinaemia.^9^ When potentially severe jaundice is suspected, a skin prick will be performed to determine TSB. The TSB level will be plotted on the Dutch nomogram^27^ (which is similar to the nomogram of the American Academy of Pediatrics and explained in box 1) and be discussed with the affiliated paediatrician, according to local procedures. If treatment for hyperbilirubinaemia is indicated, as judged by the affiliated paediatrician, the neonate will be admitted to the hospital for this purpose.

#### Intervention 1: TcB measurement as a non-invasive screening tool

During the study phase in which this intervention is tested, TcB will be measured daily starting from 24 hours of age using the Dräger JM-105, a CE-marked and validated hand-held bilirubinometer, in all included neonates admitted to a PCBC allocated to this intervention.^28–31^ If TcB exceeds the phototherapy threshold, as determined by the Dutch TSB nomogram for neonates born after 35 weeks of gestation,^9^ TSB will be quantified. Because the nomograms were originally designed to be applied to the TSB measurements and because the TcB measurements have an inaccuracy of maximally 50 µmol/L (ie, 2.9 mg/dL),^14 32^ TSB will also be quantified if TcB is less than 50 µmol/L below the phototherapy treatment threshold. The TSB level obtained will be discussed with an affiliated paediatrician (of the nearby hospital) in order to determine the need for phototherapy, again based on the Dutch nomogram.^9^ A second TcB measurement on the same day may be performed at the discretion of the maternity care professional (eg, if the TcB level is close to the threshold for measuring TSB).

Following institution of phototherapy, bilirubin levels will be monitored using TSB rather than TcB given the reduced reliability of TcB in neonates receiving or having received phototherapy.^14^
Box 1The Dutch TSB nomogram^27^
The Dutch total serum bilirubin (TSB) nomogram has the same values as the nomogram of the American Academy of Pediatrics. The nomogram consists of three risk categories: lower risk, medium risk and higher risk. The risk assessment is based on the gestational age and several risk factors (blood group antagonism, other haemolytic disease, birth asphyxia, suspicion of infection/sepsis, the neonate being ill or drowsy and serum albumin level below 30 g/L). The need for phototherapy and exchange transfusion depend on the risk assessment and the postnatal age of the neonate. A translated version of the Dutch TSB nomogram is depicted in figure 1.

